# Biomarkers of Airway Disease, Barrett’s and Underdiagnosed Reflux Noninvasively (BAD-BURN) in World Trade Center exposed firefighters: a case–control observational study protocol

**DOI:** 10.1186/s12876-024-03294-9

**Published:** 2024-08-09

**Keywords:** Air pollutants, Airway hyperreactivity, Ambient particulate matter, Barrett’s esophagus, Gastro-esophageal reflux disease, Particulate, Aerodigestive

## Abstract

**Background:**

Particulate matter exposure (PM) is a cause of aerodigestive disease globally. The destruction of the World Trade Center (WTC) exposed first responders and inhabitants of New York City to WTC-PM and caused obstructive airways disease (OAD), gastroesophageal reflux disease (GERD) and Barrett’s Esophagus (BE). GERD not only diminishes health-related quality of life but also gives rise to complications that extend beyond the scope of BE. GERD can incite or exacerbate allergies, sinusitis, bronchitis, and asthma. Disease features of the aerodigestive axis can overlap, often necessitating more invasive diagnostic testing and treatment modalities. This presents a need to develop novel non-invasive biomarkers of GERD, BE, airway hyperreactivity (AHR), treatment efficacy, and severity of symptoms.

**Methods:**

Our observational case-cohort study will leverage the longitudinally phenotyped Fire Department of New York (FDNY)-WTC exposed cohort to identify *Biomarkers of Airway Disease, Barrett’s and Underdiagnosed Reflux Noninvasively (BAD-BURN)*. Our study population consists of *n =* 4,192 individuals from which we have randomly selected a sub-cohort control group (*n =* 837). We will then recruit subgroups of *i.* AHR only *ii.* GERD only *iii.* BE *iv.* GERD/BE and AHR overlap or *v.* No GERD or AHR, from the sub-cohort control group. We will then phenotype and examine non-invasive biomarkers of these subgroups to identify under-diagnosis and/or treatment efficacy. The findings may further contribute to the development of future biologically plausible therapies, ultimately enhance patient care and quality of life.

**Discussion:**

Although many studies have suggested interdependence between airway and digestive diseases, the causative factors and specific mechanisms remain unclear. The detection of the disease is further complicated by the invasiveness of conventional GERD diagnosis procedures and the limited availability of disease-specific biomarkers. The management of reflux is important, as it directly increases risk of cancer and negatively impacts quality of life. Therefore, it is vital to develop novel noninvasive disease markers that can effectively phenotype, facilitate early diagnosis of premalignant disease and identify potential therapeutic targets to improve patient care.

**Trial registration:**

Name of Primary Registry: “Biomarkers of Airway Disease, Barrett's and Underdiagnosed Reflux Noninvasively (BADBURN)”. Trial Identifying Number: NCT05216133. Date of Registration: January 31, 2022.

**Supplementary Information:**

The online version contains supplementary material available at 10.1186/s12876-024-03294-9.

## Background

Particulate matter (PM) exposure is a risk factor for aerodigestive disease and mortality [1–3]. On September 11, 2001 (9/11), first-responders and inhabitants of New York City were exposed to World Trade Center (WTC)-PM [4–35]. Many subsequently developed aerodigestive diseases including obstructive airways disease (OAD), gastroesophageal reflux disease (GERD) and Barrett’s Esophagus (BE) [23, 34, 36–42]. By 2005, approximately 44% of WTC rescue and recovery workers had developed GERD, which is 8.2-fold higher than the pre-9/11 prevalence, and more than double the general US population [43–46]. After WTC-PM exposure, GERD occurred more often in asthmatics [42]. Comorbid aerodigestive disease affected 51.4% of firefighters [47].

GERD and BE are risk factors for esophageal adenocarcinomas (EAC) [48]. Patients with BE face at least 30-fold higher risk of developing EAC than the general population [49, 50]. Complications of GERD extend beyond malignancy and can adversely affect quality of life (QoL), impair productivity, and lifespan [46, 51–53]. GERD can incite or exacerbate co-morbidities such as allergies, sinusitis, chronic bronchitis, and asthma [54]. There is a 59.2% prevalence of GERD symptoms in patients with asthma compared to 38.1% in controls [55]. GERD treatment in WTC responders with proton pump inhibitors (PPIs) have been found to increase risk of severe cognitive impairment [56]. Cognitive decline with PPI use has also been reported in the general population [57].

Despite numerous studies suggesting potential interdependence between airway and digestive diseases, the underlying causative factors and mechanisms remain unclear [55]. Biomarkers are often key to identifying causative pathways and mechanistic targets. While some studies have investigated serum, salivary, and microbial biomarkers of GERD, they are often not focused on the contribution of respiratory disease [58–60].

The availability of clinical longitudinal phenotyping makes the WTC-PM exposed Fire Department of New York (FDNY) first responders cohort ideal for biomarker discovery [10, 22, 28–31, 61–65]. Notably, we have successfully identified biomarkers associated with GERD and BE in a pilot population with respiratory disease, facilitating the identification of biologically relevant immune pathways [3].

The diagnosis of GERD itself is a complex process that relies on subjective clinical symptoms and often necessitate objective but invasive testing such as endoscopy and 24-h pH monitoring [66]. Those with endoscopic evidence of reflux may be entirely asymptomatic, potentially leading to under-diagnosis of patients at risk of BE and EAC [67, 68]. Even with the most invasive procedures, the diagnosis of GERD can be elusive and plagued by poor sensitivity [69].

In light of this, we propose to explore noninvasive biomarkers that could identify a population of aerodigestive disease, enabling better phenotyping of FDNY-WTC cohort with aerodigestive disease. In addition to their diagnostic utility, noninvasive biomarkers may direct future research into mechanisms and their downstream effects. GERD/BE biomarkers are also important to identify in the clinically silent presentations [69]. Additionally, we will identify novel non-invasive biomarkers of aerodigestive disease through a multi-OMIC approach. We will profile not only the metabolome and microbiome, but also exhaled, secreted, and blood biomarkers of aerodigestive disease Fig. 1 [70].

**Fig. 1 Fig1:**
[figure not shown]
Overview of planned biomarker assessments

To address a critical gap in the current literature, we will 1. *Quantify noninvasive measures* of aerodigestive disease (salivary pepsin, serum biomarkers/metabolome, fractional exhaled nitric oxide (FeNO), exhaled breath condensate (EBC), microbiome, cognitive measures and aerodigestive QoL/disease severity measures to phenotype and assess treatment efficacy. 2. *Develop and optimize* a noninvasive biomarker model of aerodigestive disease and also 3. Determine the effect of aerodigestive disease on QoL, cognition and symptom phenotype.

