## Methods/design

### Study design and participants

The FDNY WTC-health program (WTC-HP) electronic medical record (EMR) will be used to obtain clinical variables such as age, gender, years of FDNY service, WTC site exposure level, and lung function measures, as previously described [22, 27, 62–65, 71]. Our observational study is NYU IRB Approved # 21–00679 and available at clinicaltrials.gov #NCT05216133. Study Definitions and Inclusion/Exclusion Criteria can be found in Table 1.

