**Fig. 2 Fig2:**
[figure not shown]
Study design

*Recruited Cohort* will be developed to assess for noninvasive biomarkers. We will recruit a subset *N =* 40/group (*i.* AHR only *ii.* GERD only *iii.* BE *iv.* GERD/BE and AHR overlap or *v.* No GERD nor AHR) from the sub-cohort, Fig. 2. Recruitment strategies will include: i. Direct mailings; ii. Email (potential participants will be sent the same IRB-approved recruitment message to their personal emails using end-to-end encryption; iii. Study website will include recruitment messages providing general information on the study and answers to frequently-asked questions. No direct communications will be made with participants through the website, and no PHI will be used or available within the study website; iv. Telephone contact. A description of the study will be provided to potential participants and, upon their expression of interest, the investigator will perform an eligibility screening. In addition to meeting the inclusion criteria as outlined above, participants should: i. have available serum from their first post 9/11 WTC-HP ii. Not currently be receiving treatment for malignancy iii. Have no limitations to a minimal risk blood draw iv. Be willing and able to sign consent; and v. be able to attend a single-visit.

All co-investigators have received training from the principal investigator in how to obtain consent and answer questions that may arise during the consent process. The consent and letter have been written to comply with the requirement that they be written at a 5th grade reading level, evaluated by the Flesch–Kincaid readability test. In addition, subject will be asked to provide their understanding of what the study is about at the time of the consenting process. English is the primary language of all FDNY rescue workers, see Appendix.

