### Case status

*WTC-AHR* will be defined as having a positive methacholine (PC_200_ < 16), or a positive bronchodilator response (by ATS/ERS guidelines with improvement of FEV_1_ by 12% and at least 200 mL) at least once post-9/11 [73, 74] and/or EMR diagnosis. *GERD* will be defined as: biopsy-proven erosive esophagitis LA grade C or D; stricture or Barrett’s esophagus on endoscopy; and/or esophageal acid exposure time > 6% on a pH or pH impedance study. GERD will also be defined on EMR diagnosis and/or PPIs, H_2_ blockers, antacid, or surface agent use [75]. *BE*, as a subset of GERD, will have any of the following additional inclusion criteria: biopsy-proven columnar epithelium lining ≥ 1 cm of the distal esophagus with intestinal metaplasia characterized with goblet cells on histology; diagnosis on EMR, Tables 2 and 3 [75]. The recruited participants will be consented prior to any research activity and measurement visit via REDCap software or in person.

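### Aim 1 and the abstract promise to assess treatment efficacy, but an observational, single-visit study grouped by disease can show only association with current treatment

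*Protocol article*

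**What the plan says.** **Purpose.** Background, first numbered aim: the measures are collected as "aerodigestive QoL/disease severity measures to phenotype and assess treatment efficacy". Abstract, Methods: the subgroups are phenotyped "to identify under-diagnosis and/or treatment efficacy". The Abstract's Background paragraph names treatment efficacy among the things that need biomarkers. The Discussion's paragraph on serum says that such biomarkers will be assessed there too.

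**Design.**
- Study design and participants: "Our observational study is NYU IRB Approved". No treatment is allocated.
- Study population, Recruited Cohort: "We will recruit a subset *N =* 40/group". The five groups are defined by AHR, GERD and BE status. Participants must "be able to attend a single-visit" and must have banked serum from their first programme visit after 9/11.
- Case status: besides endoscopic and pH-study criteria, "GERD will also be defined on EMR diagnosis and/or PPIs, H_2_ blockers, antacid, or surface agent use".
- Model building: mixed-effects and joint models of biomarkers over time, directed at time trends and the risk of developing disease.
- Statistical Analysis: the only test that names a treatment compares bronchodilator (SABA and LABA) use across the disease groups.
- Discussion, salivary pepsin paragraph: pepsin measurements are said not to be affected by concurrent PPI use.
- Data safety monitoring: refers to a study intervention and to intention-to-treat.

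**The concern.** An efficacy statement needs either treated and untreated people who were comparable before treatment, or measurements before and after treatment starts. For most of the measures in Aim 1 the article describes neither. People who take acid suppression or bronchodilators generally take them because of their disease, so a difference between users and non-users at one visit mixes drug effect with the severity that led to prescribing. That mixture can have the wrong sign.

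What is at stake is the conclusion the study may draw, not its diagnostic aims. The Background already cites reports of cognitive harm with PPIs, and the study measures cognition and quality of life. A difference by current treatment, reported under an aim labelled efficacy, could be read as a finding about those drugs.

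**Working it through.** **1. Is there a before-and-after measure?** The measures listed in Aim 1 compare as follows.

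| Measure | Earlier value described? | Tied to treatment start? |
|---|---|---|
| Salivary pepsin, FeNO, breath condensate, microbiome | No | No |
| Questionnaires, cognition | No | No |
| Serum proteins and metabolome | Yes: first post-9/11 programme visit | Not stated |

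Limitations and potential study concerns says the serum was banked within six months of 9/11 and places the study in the second decade after exposure. Change between the two serum samples therefore combines ageing, disease onset and any treatment. The longitudinal models name time, confounders and disease risk, but no treatment term.

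**2. Is there a treated-versus-untreated comparison?** Groups are formed by disease. Under Case status, PPI, H2-blocker, antacid or surface-agent use is enough for GERD status. Two things follow. GERD cases who qualify only by medication are all treated, so none of them has an untreated counterpart. Users of these agents also cannot be in the groups without GERD, so comparing users with non-users across groups is partly a comparison of GERD with no GERD.

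**3. Could pepsin show response?** It is the first listed item under Outcomes. By the article's own account PPI use does not affect it, so on that account it cannot register a PPI effect.

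**4. Does the sample size cover a treatment contrast?** First, the plan's own figure. Inputs from Power analysis are 40 per group, 0.78 SD and significance level 0.01 with a two-sample t-test (taken as two-sided).
- Normal approximation: 0.78 / √(2/40) = 0.78 / 0.2236 = 3.488, and 3.488 − 2.576 = 0.912, which gives 81.9% power.
- Noncentral t: 79.9% power, with a detectable difference of 0.781 SD at 80%.

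The stated 80% is reproduced, but it applies to two disease groups of 40. The article gives no treated share. Assuming that 50% to 90% of one group of 40 are treated, the difference detectable with 80% power (noncentral t, standard error SD × √(1/n1 + 1/n2)) is:

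| Treated / untreated | Level 0.01 | Level 0.05 |
|---|---|---|
| 20 / 20 | 1.13 SD | 0.91 SD |
| 28 / 12 | 1.23 SD | 0.99 SD |
| 32 / 8 | 1.41 SD | 1.14 SD |
| 36 / 4 | 1.88 SD | 1.52 SD |

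**5. How could severity distort such a contrast?** This is an illustration only; all values are assumed. Apparent deficit in the treated = starting gap − true benefit. With a true benefit of 0.3 SD:
- gap 0.2 SD: 0.2 − 0.3 = −0.1, so the treated appear 0.1 SD better;
- gap 0.5 SD: 0.5 − 0.3 = 0.2, so they appear 0.2 SD worse;
- gap 0.8 SD: 0.8 − 0.3 = 0.5, so they appear 0.5 SD worse.

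**The case against.** The best defence is that the phrase is loose wording rather than a causal claim. The article specifies no treated-versus-untreated contrast and no drug-effect estimate, and it pairs the phrase with under-diagnosis in the abstract and with undertreated cases under Model building. It may simply mean markers of how well disease is controlled. That reading is plausible, and it is why a change of wording is enough. It does not make the wording right: efficacy is named as a purpose in the aims and the abstract, and a later analysis plan cannot add allocation, or a baseline for measures taken only once.

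Three stronger readings are tempting, and the document does not support them.
- *That there is no earlier measure at all.* Banked serum is required, Blood sampling has proteins and metabolomics profiled on all samples, and longitudinal models are planned. The gap for serum is that nothing links it to treatment start.
- *That GERD cases in general are defined by drug use.* It is one route beside endoscopy, pH study and record diagnosis. It is not a stated criterion for AHR, nor one of the additional BE criteria. The share of medication-only cases is not given.
- *That the study will issue a verdict on PPIs, biased by a known amount.* No such analysis is described, and the illustrative SD values carry no information from this study.

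**Conclusion.** The stated purpose exceeds what the design can deliver. The study can describe how biomarkers, symptoms and quality of life differ by current treatment; it cannot say whether treatment works. This follows from three stated features: no allocation, groups formed by disease, and one visit for most Aim 1 measures. Early serum does not rescue the aim as written, and the GERD definition makes it harder to meet for medication-only cases.

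The size of any bias is not known. The one quantity tied to the plan is power: 0.78 SD does not carry over to a split within a group of 40, where the detectable difference at level 0.01 is 1.13 to 1.88 SD if 50% to 90% are treated. The conclusion does not depend on that range. It does assume that the schedule and endpoint tables, which cannot be read here, agree with the single visit described in the text. The diagnostic and phenotyping aims are not affected.

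**What to change.** 1. Replace treatment efficacy in the Abstract (Background and Methods), in Aim 1 and in the Discussion's serum paragraph with: association of biomarkers, symptoms and QoL with current treatment use. State that it is reported as a cross-sectional, non-causal association.
2. Add a sensitivity analysis limited to GERD cases established by endoscopy, pH study or record diagnosis, leaving out those who qualify by medication use alone.
3. Reconcile the reference to intention-to-treat and a study intervention under Data safety monitoring with the observational design.

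Cost: edits in four places plus one sentence, and one added analysis. No new data collection should be needed, because Measurement visit already includes medication history and the route to GERD status should be known from classification. The claim becomes more modest, and the sensitivity analysis uses fewer than 40 per affected group, by a number the article does not allow one to estimate.

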## Methods/design

### Study design and participants

The FDNY WTC-health program (WTC-HP) electronic medical record (EMR) will be used to obtain clinical variables such as age, gender, years of FDNY service, WTC site exposure level, and lung function measures, as previously described [22, 27, 62–65, 71]. Our observational study is NYU IRB Approved # 21–00679 and available at clinicaltrials.gov #NCT05216133. Study Definitions and Inclusion/Exclusion Criteria can be found in Table 1.

**Table 1 Tab1:**
[figure not shown]
Inclusion and exclusion criteria

*FDNY* New York City Fire Department, *WTC* World Trade Center, *COPD* Chronic Obstructive Pulmonary disease, *FEV1* Forced expiratory volume in the first second, *LLN* lower limit of normal, *WTC-HP* World Trade Center Health Program, *PC20* provocative concentration of Methacholine, *AHR* airway hyperresponsiveness, *ATS/ERS* American Thoracic Society/European Respiratory Society, *EMR* Electronic Medical Record, *GERD* Gastroesophageal Reflux Disease, *BE* Barrett’s Esophagus

### Study oversight

It will be the responsibility of the principal investigator to oversee the safety of the study at his/her site. This safety monitoring will include careful assessment and appropriate reporting of adverse events, as well as the construction and implementation of a site data and safety-monitoring plan (Study Auditing, Monitoring and Inspecting). Medical monitoring will include a regular assessment of the number and type of adverse events. All modifications will be communicated to the IRB and will be reviewed.

### Data safety monitoring

The principal investigator will be responsible for overall data safety monitoring. The following data points will be monitored: Adverse events (AE) will be monitored. Data safety monitoring reviews will be conducted yearly to ensure the safety of subjects. There are no predefined halting rules in place. We do not foresee temporary suspension of enrollment and/or study intervention due to the intent to treat nature of the study intervention. Data Monitoring Committee is not needed due to minimal risk study.

### Study population

#### Source cohort

All participants in the WTC-HP (*n =* 14,976) were screened, Fig. 2. *Inclusion Criteria:* i. Actively consented and enrolled member of the WTC-HP. ii. Pre-9/11 spirometry with Forced Expiratory Volume in 1 s (FEV_1_) ≥ Lower Limit of Normal (LLN) iii. Male Firefighter status on 9/11 with exposure at the WTC-site and entry into WTC-HP before the site closure on 7/24/2002. *Exclusion Criteria:* i. lung disease prior to 9/11 as defined by positive methacholine or bronchodilator test, or FEV_1_ < LLN. ii. Not part of initial cohort in data extraction from August 1, 2017 [72]. After all inclusion/exclusion criteria applied, the baseline cohort consists of *n =* 4,192. *Sub-cohort Development.* A representative cohort of 20% was randomly selected (*n =* 837; SPSS v. 28) from the above baseline cohort, Fig. 2.

**Fig. 2 Fig2:**
[figure not shown]
Study design

*Recruited Cohort* will be developed to assess for noninvasive biomarkers. We will recruit a subset *N =* 40/group (*i.* AHR only *ii.* GERD only *iii.* BE *iv.* GERD/BE and AHR overlap or *v.* No GERD nor AHR) from the sub-cohort, Fig. 2. Recruitment strategies will include: i. Direct mailings; ii. Email (potential participants will be sent the same IRB-approved recruitment message to their personal emails using end-to-end encryption; iii. Study website will include recruitment messages providing general information on the study and answers to frequently-asked questions. No direct communications will be made with participants through the website, and no PHI will be used or available within the study website; iv. Telephone contact. A description of the study will be provided to potential participants and, upon their expression of interest, the investigator will perform an eligibility screening. In addition to meeting the inclusion criteria as outlined above, participants should: i. have available serum from their first post 9/11 WTC-HP ii. Not currently be receiving treatment for malignancy iii. Have no limitations to a minimal risk blood draw iv. Be willing and able to sign consent; and v. be able to attend a single-visit.

All co-investigators have received training from the principal investigator in how to obtain consent and answer questions that may arise during the consent process. The consent and letter have been written to comply with the requirement that they be written at a 5th grade reading level, evaluated by the Flesch–Kincaid readability test. In addition, subject will be asked to provide their understanding of what the study is about at the time of the consenting process. English is the primary language of all FDNY rescue workers, see Appendix.

Participant-related study information will be identified through the Patient Identification Number (PID) on all participant Case Report Forms (CRFs). Participant names or other personally-identifying information will not be used on any study documents. All study-related documents will be kept in double-locked, limited access areas at each study site. A log that links the names of participants to their PID numbers will also be kept under double locks separate from all other research records, accessible only to the study staff. Original source documents for individual participants will be maintained at the FDNY-BHS and will be accessible only to study staff.

